## Methods

### Design

This study is approved by the Kaiser Permanente Northwest (KPNW) Internal Review Board (IRB) in Portland, Oregon. This study is a randomized controlled trial (RCT), with participants blinded to the type of CBM they receive (low vs. high ratio) but not blinded regarding receipt of AP contacts. All evaluators are blinded to participant study condition.

Participants will be randomized via computer-programming to one of three arms in a 1:1:1 ratio, stratified by age at recruitment (< age 15 vs. > = age 15) and minority status (white non-Hispanic vs. all others). Assignment will be conducted with computer-generated random block sizes of 6 or 9, masked from study staff.

Arm 1 is a Low-Ratio version of the CBM intervention, nearly indistinguishable from the other CBM version but with a lower proportion of trials that shift attention to the neutral stimuli (details below). Arm 2 is a High-Ratio CBM program, with a higher proportion of trials shifting attention to the neutral stimuli. Arm 3 is the same High-Ratio CBM program but with a component consisting of adherence promoting (AP) telephone calls from a study phone coach, from 1 to 4 total as needed. All CBM programs are self-administered on participants’ home computers.

The primary clinical outcome will be diagnostic remission at 6-month follow-up from all anxiety diagnoses present at baseline, as confirmed by the Anxiety Disorders Interview Schedule (ADIS) (see below). The secondary clinical outcomes will be the PARS, SCARED, attention bias, depression (PHQ-9), psychopathology severity (CGI-S), and psychosocial functioning (CGAS). We will also determine whether there are differences in treatment acceptability (PAQ) and satisfaction (CSQ-8). Another secondary outcome will be cost-effectiveness of the CBM intervention, as measured in incremental cost per anxiety-free-day (AFD) and cost per quality adjusted life year (QALY). Additional analyses will test whether baseline CGI-S, PHQ-9 (depression), severity of cognitive bias (ADP), gender, socio-economic status, and race/ethnicity moderate the effect of the intervention on the primary outcome. Additionally, we will test whether attention bias mediates the effect of the intervention on the 6-month remission rate and anxiety outcomes (PARS and SCARED). Lastly, we will examine whether CBM process variables (i.e., number of trials [dose], acceptable error rates, reaction time) is associated with CBM outcomes.

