##### Preliminary data evaluation

Prior to conducting data analyses, we will audit the data for completeness and quality, including missing data. We will evaluate distributions to ensure that they meet assumptions of planned analyses (see below), including the detection of outliers.

We will use a two-tailed α = .05 for the analyses of the primary outcomes. For the secondary outcomes, we will account for multiple testing by controlling the false discovery rate (10%) using the Benjamini–Hochberg procedure. All analyses will be carried out using the intent-to-treat principle by including all participants in analyses and their original arm assignments.

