##### Statistical analysis

For each continuous outcome (anxiety symptoms [PARS, SCARED], depression [PHQ-9], psychopathology severity [CGI-S], psychosocial functioning [CGAS]) we will test whether there are differences between arms in the trajectories across time by fitting growth curve models in a nested two-level hierarchical linear model (HLM [64–66];).We will test the primary outcome (anxiety remission based on ADIS-C) and the CGI-I with a generalized form of HLM, using a logit link and the binomial distribution. For all HLM models, the first level of the model represents within-person variation and will include time as a predictor (3–5 timepoints, depending on the measure). The second model level represents between-person variation and includes dummy indicators for arm as the predictor variables. A significant coefficient for arm on the slope of time indicates (i.e., the cross-level interaction of arm by time) that there are different trajectories across time for each arm and will be followed with a graph to interpret the interaction(s). Assuming that the trajectories are nonlinear as is common in clinical trials (e.g., initial intervention effect upon completing the intervention and maintenance period), we will use fractional polynomials to estimate the most appropriate function for time [67, 68]. We will test our primary hypotheses using linear contrasts of the dummy vectors representing treatment arm to determine whether both High-Ratio CBM arms (2 and 3) have a different trajectory than the Low-Ratio arm, and whether High-Ratio CBM + AP (Arm 3) has a different trajectory than High-Ratio CBM Only (Arm 2). Differences at 1 month in acceptability (PAQ) and client satisfaction (CSQ-8) will be tested with a one-way ANOVA with treatment arm as the independent variable and the same a priori contrasts described above.

We will conduct the moderator analyses by adding the moderator and moderatorXarm product in the level-two HLM equation discussed above. A significant coefficient for the interaction term on the slope of time would indicate a moderator effect and will be followed up with graphs of the simple effects to determine the nature of the effect modification.

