We conducted power analyses for the primary outcome (via PASS software [77]) to generate the sample required to detect the hypothesized contrasts in a logistic regression model. For our main comparison of the two High-Ratio CBM conditions versus Low-Ratio CBM, with α = .05, we would have 80% power to detect a 20% greater remission (odds ratio = 2.90) in arms 2 + 3 compared to the Low-Ratio arm with 187 participants (n~ 63 per arm) at the 6-month follow-up**.** For the comparison of the two High-Ratio CBM conditions, at an alpha level of .05, we would have 80% power to detect a 16% greater remission (odds ratio = 1.94) in the CBM + AP arm compared to the CBM only arm with 148 participants per arm (*N* = 444 total) at the 6-month follow-up. We based our target sample on the larger N needed to adequately test this latter hypothesis (Arm 2 vs. Arm 3). To compensate for the loss in precision from imputing data for those lost to follow-up, we inflated the target sample size based on an attrition rate of ~ 10% (*N* = 498, or *n* = 166 per arm). This is a conservative adjustment, as the SEs from imputed data results will be less than the SEs from a complete case analysis.

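### The outcome models are specified with arm as the only person-level predictor, so the two stratification factors are left out of all of them and baseline severity is left out of the remission model; a possible power gain is forgone

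*Protocol article*

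**What the plan says.** The Statistical analysis section gives one specification for every hierarchical model, including the logit-link model for remission. Time is the level-one predictor. At level two, "The second model level represents between-person variation and includes dummy indicators for arm as the predictor variables". Two other places suggest that this is the whole base model:

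- The moderator analyses are built by adding the moderator and its product with arm to that level-two equation, so those baseline variables are not already in it.
- The mediation model does name a baseline covariate (baseline attention bias), so the article states adjustment where it intends it.

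The Design section says that randomisation is "stratified by age at recruitment (< age 15 vs. > = age 15) and minority status (white non-Hispanic vs. all others". Race/ethnicity appears later only as a moderator; age group appears in no model.

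The Design section defines the primary outcome as 6-month remission from all anxiety diagnoses present at baseline. Under Population and recruitment, an ADIS-confirmed anxiety diagnosis is an entry requirement.

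The Power analyses section used PASS "to generate the sample required to detect the hypothesized contrasts in a logistic regression model" and mentions no covariates. The contrast that set the sample size has "80% power to detect a 16% greater remission (odds ratio = 1.94) in the CBM + AP arm compared to the CBM only arm", with 148 per arm. On error rate, "We will use a two-tailed α = .05 for the analyses of the primary outcomes".

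**The concern.** Two things do not fit together.

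First, stratified randomisation balances the arms on age group and minority status. If those factors predict outcome, a model that omits them does not credit that balance: its standard errors are somewhat too large and the test is slightly conservative. The analysis then does not reflect the randomisation.

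Second, baseline status on the primary outcome carries no information, because everyone is unremitted at T0. The definition of remission nevertheless makes baseline severity a natural predictor: a participant with three diagnoses must lose three, and one with a single diagnosis must lose one. The number of baseline ADIS diagnoses, PARS, SCARED and CGI-S are all available at T0 (Table 1), and the primary model uses none of them.

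At stake is precision on the Arm 3 versus Arm 2 contrast, which fixed the sample size and was planned at 80% power with little to spare.

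**Working it through.** **Inputs from the article.** Two-sided α = 0.05; 80% power; a 16-point difference with odds ratio 1.94; 148 per arm; about 10% attrition; 166 per arm enrolled. **Assumed, because the article does not give it:** the share of outcome variance (R²) explained by the strata and baseline severity.

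**Step 1: reproduce the planned sample size without covariates.** A 16-point difference with odds ratio 1.94 implies rates of 0.341 and 0.501 (or the mirror pair 0.499 and 0.659, which gives the same result). Check: (0.501/0.499)/(0.341/0.659) = 1.94. With the pooled two-proportion formula and p̄ = 0.421,

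n = [1.960·√(2·p̄(1−p̄)) + 0.842·√(p₁(1−p₁) + p₂(1−p₂))]² / 0.16² = 148.3, rounded up to 149 per arm.

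Power at 148 per arm is 79.9%. The stated figure is therefore an unadjusted one, and the arm-only comparison delivers it.

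**Step 2: approximate power with covariates at 148 per arm.** The planned non-centrality is 1.960 + 0.842 = 2.80. Adjustment divides it by √(1−R²), and power is Φ(2.80/√(1−R²) − 1.96).

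| Assumed R² | Power |
|---|---|
| 0 | 80.0% |
| 0.05 | 82.0% |
| 0.10 | 84.0% |
| 0.15 | 86.0% |

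**Step 3: check by simulating the logistic model.** Settings: 148 per arm, marginal rates 0.342 and 0.502, one standard-normal covariate, 6,000 replicates, Wald tests.

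| Odds ratio per SD | R² | Unadjusted | Adjusted |
|---|---|---|---|
| 1.00 | 0.00 | 80.6% | 80.1% |
| 1.28 | 0.01 | 80.8% | 81.0% |
| 1.65 | 0.05 | 80.9% | 82.2% |
| 2.12 | 0.10 | 80.8% | 84.6% |
| 2.72 | 0.16 | 79.8% | 86.5% |
| 4.48 | 0.28 | 81.0% | 91.1% |

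The approximation holds over the range used. With weak covariates the gain is within about a point of zero.

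**Step 4: where baseline is already used.** The article counts 3–5 timepoints per measure. Table 1 gives PARS and SCARED five waves, and ADIS three, only if T0 is included. The growth models for PARS, SCARED, PHQ-9 and CGAS therefore already hold each measure's own baseline as the first repeated value. The absence of baseline severity is specific to remission.

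**Step 5: does the gain carry over to the arm-by-time slope?** A person-level main effect explains differences in level between participants, not differences in change. In a simulated linear growth model (148 per arm, five waves, a strongly prognostic covariate on the intercept), the standard error of arm by time was 0.0418 both with and without the covariate. The figures in Steps 2 and 3 therefore belong to a single 6-month comparison, which is what the power calculation describes.

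**Step 6: compare with attrition.** The article states that "we inflated the target sample size based on an attrition rate of ~ 10"%. After that loss, 166 × 0.9 = 149.4 per arm remain, and 2.80·√(149.4/148) gives 80.4% power, so the plan already covers it. With no loss at all (166 per arm) power would be 84.3%. Starting from 149.4 per arm, R² = 0.05 gives 82.3%, R² = 0.10 gives 84.3% and R² = 0.15 gives 86.3%. Adjustment thus falls short of full retention at 0.05, matches it at 0.10 and exceeds it only above that.

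**The case against.** The strongest reply is that a covariate list is ordinarily left to the statistical analysis plan, and that saying a level includes arm indicators does not rule out other terms. This has some force, and an unseen plan may add covariates. But the article does more than stay silent: it states the level-two predictors for all the hierarchical models, and it describes baseline variables as additions made for the moderator tests. A plan that adjusted the main tests would depart from the published specification.

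Other parts of the reply stand and limit the point:

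- A reader might infer that the trial is underpowered. It is not on this account: the stated 80% was calculated without covariates and reproduces, and omitting the strata causes no bias in the comparison.
- A reader might infer that every outcome model ignores baseline severity. The timepoint count shows otherwise for the continuous growth models.
- A reader might infer that adjustment would more than make up for attrition. The sample size already allows for about 10% loss, and against full retention that statement fails at R² = 0.05 and only breaks even at 0.10.
- Covariate main effects buy essentially nothing on the trajectory contrasts.
- The prognostic strength of these variables is not documented, so the size of the gain cannot be asserted.

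**Conclusion.** The point holds as an improvement forgone, not as an error in a stated figure. As written, the main models omit both stratification factors, and the primary remission model takes nothing from baseline severity despite a definition of remission that depends on the diagnoses held at baseline. The analysis is unbiased and reaches its planned 80%.

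For the 6-month Arm 3 versus Arm 2 comparison at 148 per arm, adjustment would bring power to about 82%, 84% or 86% at R² of 0.05, 0.10 or 0.15, and leave it near 80% if the covariates are weak. This rests on the article's own rates and α, on an assumed R², and on a single-timepoint logistic comparison rather than an arm-by-time slope.

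**What to change.** - **Primary 6-month remission comparison:** prespecify as covariates the two stratification factors (age group, minority status) and baseline severity, for example the number of baseline ADIS anxiety diagnoses, the PARS total, or both. Fix the choice before unblinding.
- **Reporting:** give a standardised (marginal) risk difference beside the adjusted odds ratio. The adjusted odds ratio is conditional on the covariates and is not directly comparable with the planning value of 1.94, whereas the risk difference can be set against the planned 16 points.
- **Secondary models:** include the two stratification factors for consistency with the randomisation, without claiming a precision gain on the arm-by-time slopes.

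The cost is a change of analysis wording. All the variables are collected at baseline, and no extra participants or assessments are needed.

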### Assessments

After the preliminary screening call, interested and potentially eligible participants will complete a baseline interview where final eligibility is determined. All measures at baseline will be administered to parent and youth participants over the phone, prior to randomization. See Table 1 for the assessment schedule.

**Table 1 Tab1:** Assessment Schedule

Measures	Administration time (mins)	Respondent	Youth or Parent Sx	Timepoints*					
				S	T0	T1	T2	T3	T4
Phone eligibility screen	15	Y P	Y	x					
Youth Anxiety measures									
Anxiety Dx Interview Schedule-Child (ADIS-C)**	50	Y P	Y		x			x	x
Pediatric Anxiety Rating Scale (PARS)	15	Y P	Y		x	x	x	x	x
Screen Child Anxiety Relate Emotional Dx (SCARED)	10	Y P	Y		x	x	x	x	x
Child Avoidance Measure–Self Report (CAMS)	5	Y	Y		x	x	x	x	x
Child Avoidance Measure–Parent Report (CAMP)	5	P	P		x	x	x	x	x
Depression measures									
Patient Health Questionnaire (PHQ-9)	10	P	Y		x	x	x	x	x
Patient Health Questionnaire (PHQ-9) (Parent self-report)	5	P	P		x	x	x	x	x
Other psychopathology, improvement measures									
Clinical Global Improvement –Severity (CGI-S)	5	Y	Y		x				
Clinical Global Improvement –Improvement (CGI-I)	–	Y	Y			x	x	x	x
Psychosocial functioning, quality of life measures									
Children’s Global Adjustment Scale (CGAS)	–	Y	Y		x	x	x	x	x
Healthcare services, economic measures									
Child & Adolescent Services Assessment (CASA)	5–10	Y P	Y			x	x	x	x
EQ5D	5	Y P	Y		x	x	x	x	x
Other measures									
Demographics	5	P	–		x				
State Trait Anxiety Inventory (STAI) – State	5	P	P		x	x	x	x	x
Peterson Pubertal Development Scale (PDS)	5	Y	Y		x				
Insomnia Severity Index (ISI)	5	Y	Y		x	x	x	x	x
Participant Acceptability Questionnaire (PAQ)	5	Y P	–			x			
Client Satisfaction Questionnaire (CSQ-8)	5	Y P	Y			x			
U Rhode Island Change Assessment (URICA-S)	5	Y	Y		x	x			
Instrumental Variables (IV)	5	Y	Y		x				
CBM session review	5	Y	Y			x			
Treatment adherence and process data	–	–			x	x	x	x	x

*Timepoints: S = Screening; T0 = Baseline; T1 = 1-month follow-up; T2 = 3-month follow-up; T3 = 6-month follow-up; T4 = 12-month follow-up

** Primary outcome, ADIS anxiety and depression modules only

**health care utilization data obtained from the HMO administrative data system

Dx = diagnoses/disorders, Sx = symptoms, Y=Youth, P=Parent, I=Interviewer

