#### Other psychopathology, improvement

We will assess overall clinical status with the 7-point **Clinical Global Impression (CGI)** Severity and CGI-Improvement scales [42]. The CGI provides a brief assessment of the patient’s overall psychiatric illness before and after initiating a medication or treatment. The CGI-S measures the severity of illness and will be assessed at baseline. At follow-up, the CGI-I will be used as a complementary measure to assess improvement in psychiatric illness after initiating treatment. A CGI-I score of < 2 (very much or much improved) is considered a response to treatment.

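### As usually read, the growth models give each arm its own baseline mean although baseline precedes randomisation; a shared intercept would sharpen the PARS, SCARED, PHQ-9 and CGAS contrasts

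*Protocol article*

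**What the plan says.** All from the protocol article.

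- **Level 1** (Statistical analysis): the model "will include time as a predictor (3–5 timepoints, depending on the measure").
- **Waves** (Assessments, footnote to Table 1): "T0 = Baseline; T1 = 1-month follow-up; T2 = 3-month follow-up; T3 = 6-month follow-up; T4 = 12-month follow-up". Table 1 schedules PARS, SCARED, PHQ-9 and CGAS at T0 to T4. There are four follow-up waves, so a measure reaches five time points only if baseline is itself a modelled outcome.
- **Level 2** (Statistical analysis): "The second model level represents between-person variation and includes dummy indicators for arm as the predictor variables". The sentence does not confine the dummies to the slope equation.
- **Tested term** (Statistical analysis): "A significant coefficient for arm on the slope of time indicates" that trajectories differ between arms. The text calls this the cross-level interaction of arm by time. The two planned contrasts are Arms 2 and 3 against Arm 1, and Arm 3 against Arm 2.
- **Shape of time** (Statistical analysis): trajectories are expected to be nonlinear, and "we will use fractional polynomials to estimate the most appropriate function for time".
- **Timing of baseline** (Assessments): "All measures at baseline will be administered to parent and youth participants over the phone, prior to randomization".

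The article states no common intercept and no baseline covariate. It gives no variance or correlation for any continuous outcome.

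**The concern.** Because baseline is taken before allocation, the three arms share one population mean at T0, and any observed difference there is chance. A model that estimates three baseline means measures each arm's course from its own chance starting point, so that noise enters every arm-by-time contrast. A model with one shared intercept uses the known equality and so tests the same hypotheses with smaller standard errors.

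The four outcomes affected carry the hypothesis, stated in the Background, of greater improvement in symptoms and functioning. As secondary outcomes they must also pass false-discovery-rate control at 10%. Precision that the data already hold would be given up without need.

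**Working it through.** **No stated figure to reproduce.** The article gives no sample size or power for the continuous outcomes. Its 148 per arm concerns 6-month remission and is not at issue. The sample size cancels from every ratio below.

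**Assumptions.** Visits at 0, 1, 3, 6 and 12 months; equal arms; complete data; total variance 1. The correlation ρ is assumed, over 0.3 to 0.7.

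**1. Change at one visit.** With free baseline means the variance per arm is 2(1 − ρ). With a common mean it is 1 − ρ². The ratio is (1 + ρ)/2, so the reduction is (1 − ρ)/2.

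| ρ | free | common | ratio | reduction | free relative to common |
|---|---|---|---|---|---|
| 0.3 | 1.40 | 0.91 | 0.65 | 35% | 1.54 |
| 0.5 | 1.00 | 0.75 | 0.75 | 25% | 1.33 |
| 0.7 | 0.60 | 0.51 | 0.85 | 15% | 1.18 |

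At ρ = 0.5 the gain is worth one third more participants. Suppose a contrast has 80% power at two-sided 0.05 with a common mean. With free means its power is Φ(2.80 × √((1 + ρ)/2) − 1.96), which is 62%, 68% and 73% at ρ = 0.3, 0.5 and 0.7. The 0.05 level is only illustrative here, since the secondary outcomes fall under false-discovery-rate control.

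**2. Slope contrast, one time term, exchangeable correlation.** Let x be the time function at the five visits, with x = 0 at baseline, and let Sxx = Σx² − (Σx)²/5. Then

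ratio (common/free) = Sxx / [Σx² − ρ(Σx)²/(1 + 4ρ)].

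- *Linear time:* Σx = 22, Σx² = 190, Sxx = 190 − 484/5 = 93.2. At ρ = 0.5 the denominator is 190 − 484/6 = 109.3 and the ratio is 0.852. The reductions are 25%, 15% and 8% at ρ = 0.3, 0.5 and 0.7.
- *log(t + 1):* Σx = 6.590, Σx² = 12.768, Sxx = 4.082. At ρ = 0.5 the denominator is 12.768 − 43.43/6 = 5.529 and the ratio is 0.738. The reductions are 40%, 26% and 14%.

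**3. Two-term curve (√t and t), 6-month contrast, exchangeable correlation.** Generalised least squares with and without arm in the intercept gives reductions of 53%, 37% and 22%.

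**4. Random intercept and slope.** Let W = G + σ²(Z′Z)⁻¹ be the covariance of one person's estimated intercept and slope, where Z holds the constant and x, G is the random-effects covariance and σ² the residual variance. Fixing the arm difference in intercepts at zero reduces the slope variance by W₀₁²/(W₀₀W₁₁), where

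- W₀₁ = g₀₁ − σ²x̄/Sxx
- W₀₀ = g₀₀ + σ²(1/5 + x̄²/Sxx)
- W₁₁ = g₁₁ + σ²/Sxx

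Two illustrative extremes:

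- *Low.* Linear time, g₀₀ = 0.7, σ² = 0.3, random-slope variance 0.2 at month 12 (g₁₁ = 0.2/144), intercept–slope correlation +0.3. W₀₁ = 0.00935 − 0.01416 = −0.00481; W₀₀ = 0.822; W₁₁ = 0.00461. The reduction is 0.6%.
- *High.* log(t + 1), g₀₀ = 0.3, σ² = 0.7, random-slope variance 0.1 at month 12 (g₁₁ = 0.1/6.579), correlation −0.3. W₀₁ = −0.0203 − 0.2261 = −0.2463; W₀₀ = 0.738; W₁₁ = 0.187. The reduction is 44%.

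The other illustrative settings tried fall between these. The main driver is the sign of the intercept–slope correlation: a positive one offsets the second term of W₀₁, and a negative one adds to it.

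**The case against.** **The separate baseline means are not in the text.** The article does not say which level-2 equation carries arm, and the only arm coefficient it names is the one on the slope. A slope-only model, which is what the fix asks for, is compatible with the wording, and a condensed article may leave this detail to an analysis plan that is not shown. This stands as a limit: the free intercept is an inference. It is still the conventional reading of arm dummies at level 2 with an interaction. The article does specify the level-2 predictors and the tested term, and it leaves the arms unconstrained at baseline. The same sentence settles either reading.

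**A reader might infer a fixed loss of 15–35%.** The documents do not support that. The range is (1 − ρ)/2 for change at one visit over an assumed ρ, whereas the plan tests a growth-curve slope. For that slope the loss depends on ρ, the time function and the random-effects covariance, and it can be negligible.

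**A reader might extend the point to all continuous outcomes or to the primary result.** Neither holds. CGI-S is listed among the growth-curve outcomes, but "The CGI-S measures the severity of illness and will be assessed at baseline" and Table 1 schedules it only there, so it has no trajectory. Remission is binary and every participant has a qualifying diagnosis at baseline, so there is no chance imbalance in it to remove.

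**Arm-specific intercepts are a valid, standard analysis.** This stands. They cause no bias, no inflation of type I error and no change to the sample size, which rests on remission.

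**A shared intercept is safe only if the curve fits.** This also stands. With a stiff time function the fitted intercept need not equal the baseline mean, and the article itself expects an early effect followed by maintenance.

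**Conclusion.** The point holds as a conditional loss of efficiency on four secondary outcomes: PARS, SCARED, PHQ-9 and CGAS. The article establishes that baseline is modelled as an outcome, that it precedes randomisation, and that no shared intercept or baseline adjustment is stated. That each arm has a free baseline mean is the usual reading, not a quoted fact.

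No single percentage can be attached. At moderate correlation and with the nonlinear time course that the article expects, a saving of about a quarter of the variance is plausible. Linear time, or random slopes positively correlated with the intercept, would shrink it, possibly to almost nothing. The change is worth making because it is cheap and the possible gain is material, not because the planned analysis is invalid.

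**What to change.** In the Statistical analysis section, state for PARS, SCARED, PHQ-9 and CGAS that arm enters only the slope (time) equations, so that all arms share one baseline intercept. Add that the time function will be flexible enough to fit the baseline mean and the early change. Keep both planned contrasts and the direct maximum likelihood handling of missing data.

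An alternative with a similar aim is to model the follow-up visits only, with the baseline score as covariate and with an arm main effect plus arm-by-time. It is not equivalent. It needs the main effect to capture a difference already present at 1 month, and it drops participants with no follow-up visit, where the article expects about 10% attrition by 1 month.

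The cost is a sentence or two of analysis wording and a check that the chosen curve fits at baseline and 1 month. No extra data are needed. The wording should be fixed before unblinded data are examined.
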